### Data management and quality control

2.6

Patients will be required to practice rhythm-guided walking or singing until they master it on their first hospital visit. Telephone calls or video conferences by rehabilitation instructors will be integrated at the start of the program to ensure proper execution. After each training session, participant performance will be automatically transferred to the digital platform to facilitate the identification and verification of adherence to the prescribed exercise plan. Research assistants will verify training completion every day, record training adherence, and remind the patients to exercise.

To decrease measurement error, each participant will be assessed by a single nurse during different visits. Study data will be maintained on a password-protected platform and backed up to a secure external hard drive, with access restricted to authorized researchers and staff. Automatic plausibility controls will be set to detect any inconsistencies or inaccuracies during data entry.

### Statistical analysis

2.7

All statistical analyses will be performed using full intention-to-treat analyses, with scores on the dependent variables for dropouts carried-over using the multiple imputation method. Independent samples *t*-tests, chi-square tests, and F-tests will be used to analyze differences between dropouts and completers regarding baseline characteristics.

All three groups will be examined using a two-sample Student’s *t*-test for normal distributions or a Wilcoxon test for non-normal distributions (pre and postscores). The differences among the three groups at each time point (4, 8, and 12 weeks) will be analyzed using the Student’s *t*-test or Mann–Whitney U test. A two-way analysis of variance with repeated measures will be used to determine the effects of time and group on the dependent variables.

All data will be analyzed using SPSS V.21.0 (IBM) software packages. Statistical significance is set at two-sided *p* < 0.05.

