#### Sample size calculation

2.7.1

Considering the lack of previous studies combining music-guided exercise with singing, we did not perform a formal sample size calculation. Nevertheless, we calculated a sample size based on relevant studies applying similar rehabilitation interventions (27, 28). We used ISWT (the primary outcome) to calculate the sample size, as exercise capacity was one of the most sensitive outcome measures to detect the benefit of rehabilitation. We assumed that the mean changes in ISWT of multi-model MT group, rhythm-guided walking group and usual care group are 40 m, 27 m, and -15 m, respectively (27, 28), and the combined standard deviations (SD) are 35 m, 38 m, and 40 m, respectively. Based on a rate of type-I error of α = 0.05, a power of 80% (rate of type-II error of β = 0.1), and a possible dropout rate of 50%, each group will require at least 18 patients.

$$n=\frac{\psi^{2}\left(\frac{\sum S_{i}^{2}}{k}\right)}{\sum \left(\bar{X_{i}}-\bar{X}\right)\;\left(k-1\right)}$$

Therefore, 75 participants are anticipated to be enrolled into this study.

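### The missing-data rule mixes carry-forward wording with multiple imputation; read as carry-forward, it could shrink the assumed 55 m ISWT difference to about 37 m at the 50% dropout allowance

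*Protocol article*

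**What the plan says.** Section 2.7 (Statistical analysis) sets the analysis population: "All statistical analyses will be performed using full intention-to-treat analyses". The same sentence gives the missing-data rule, "with scores on the dependent variables for dropouts carried-over using the multiple imputation method".

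The section then names three kinds of analysis that would use those data:
- pre/post comparisons by t-test, or by Wilcoxon test if the data are not normal;
- between-group comparisons by visit ("The differences among the three groups at each time point (4, 8, and 12 weeks) will be analyzed using" Student's t-test or the Mann–Whitney test);
- a longitudinal test: "A two-way analysis of variance with repeated measures will be used to determine the effects of time and group on the dependent variables".

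Section 2.7.1 (Sample size calculation) allows for "a possible dropout rate of 50" per cent. It assumes that the mean ISWT changes in the multi-module, walking and "usual care group are 40 m, 27 m, and -15 m, respectively". Table 1 schedules ISWT at baseline and at weeks 4, 8 and 12. Section 2.5 makes change from baseline at those three visits the primary outcome.

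**The concern.** To carry a score over is to reuse one observed value in place of a missing one, and to treat it as if it had been measured. Multiple imputation draws several plausible values from a model, analyses each completed data set and combines the results. The sentence attaches both terms to the same missing scores. Two analysts could apply it differently and each claim to follow the protocol, and the choice could be made after data are seen.

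The missing scores include the primary outcome. At the dropout level the plan allows for, the reading chosen would move the estimated effect materially.

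The listed tests add a second difficulty. Some do not take multiply imputed data easily, which leaves an analyst a practical reason to fall back on something simpler.

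**Working it through.** **1. The plan's own figure.** Inputs from section 2.7.1: means 40, 27 and −15 m; SDs 35, 38 and 40 m; α 0.05; power 80%; dropout 50%; result 18 per group.
- Mean variance = (35² + 38² + 40²)/3 = 4269/3 = 1423.
- Grand mean = 52/3 = 17.33. Sum of squared deviations = 22.67² + 9.67² + 32.33² = 1652.7; divided by k − 1 = 2 this is 826.3. The printed formula omits the square, and unsquared deviations sum to zero, so the squared form is used here.
- With the large-sample ψ of about 2.195, n = 4.818 × 1423/826.3 = 8.3, so 9. Then 9/(1 − 0.5) = 18.

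This matches the stated 18, so the means and the 50% allowance can be taken as the plan's working assumptions. (Exact 90% power gives 12, and 12 × 1.5 is also 18, so the match does not prove which route was used.)

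**2. Assumed differences.** 40 − (−15) = 55 m; 27 − (−15) = 42 m; 40 − 27 = 13 m. I take these as week-12 differences.

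**3. The carry-forward reading.** Let d be the dropout proportion, equal in each arm and unrelated to outcome.
- Baseline carried, all dropout before week 4: dropouts contribute zero change, so the multiplier is 1 − d.
- Last value carried, dropout spread evenly over the three intervals, linear change: dropouts carry 0, 1/3 or 2/3 of the change, on average 1/3. The multiplier is (1 − d) + d/3.

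| Dropout | Value carried | Multiplier | 55 m | 42 m | 13 m |
|---|---|---|---|---|---|
| 20% | last, even dropout | 0.867 | 47.7 | 36.4 | 11.3 |
| 20% | baseline | 0.800 | 44.0 | 33.6 | 10.4 |
| 50% | last, even dropout | 0.667 | 36.7 | 28.0 | 8.7 |
| 50% | baseline | 0.500 | 27.5 | 21.0 | 6.5 |

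If half of each intervention arm but none of usual care drops out, with baseline carried, the first two differences are 40 × 0.5 + 15 = 35 m and 27 × 0.5 + 15 = 28.5 m.

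A simulation with 25 per arm (20,000 runs, 55 m contrast, baseline carried) gave mean differences of 44.0 m at 20% dropout and 27.5 m at 50%. Power was 0.99 and 0.91. For this contrast the damage is mainly to the size of the estimate, less to the chance of a significant result.

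**4. The multiple-imputation reading.** If data are missing at random and the imputation model is adequate, the expected difference stays at 55 m.

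**5. The listed tests under multiple imputation.**
- t-test: gives a mean difference and standard error, which Rubin's rules pool directly.
- Repeated-measures ANOVA: F-tests can be pooled with multi-parameter or test-statistic rules. The classical form needs all four visits, which imputed data sets supply.
- Wilcoxon and Mann–Whitney: no direct pooling.

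**6. If imputation is not carried through to the ANOVA.** At 50% dropout about 37 of 75 patients (75 × 0.5 = 37.5) would have complete data. With 12 per arm, normal-approximation power is 0.95, 0.75 and 0.14 for 55, 42 and 13 m, against 0.999, 0.97 and 0.24 with 25 per arm. If dropout is random, the expected difference stays at 55 m.

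**The case against.** The best defence is that the sentence names only one method. Nothing in the article refers to a last or baseline observation, so the carry-over phrase is probably loose wording for filling in. Imputed data sets contain all visits, so the ANOVA can be run as written. The imputation model and the pooling rules are details that a condensed article may leave to the analysis plan. A mixed model and multiple imputation both rest on missing at random, so preferring one is partly a matter of judgement.

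Most of this stands, and it rules out four stronger readings that a reader might infer:
- *The tests cannot be pooled.* Not so in general: t-tests pool directly and F-tests by special rules. Only the rank tests lack a direct route.
- *The effect would be halved.* Only if carry-forward is used, dropout reaches 50% in every arm and all of it falls before week 4.
- *The analysis rests on completers.* The plan states intention-to-treat. Completers appear only in a comparison of baseline characteristics with dropouts.
- *Half the patients are expected to drop out.* The 50% is a planning allowance, not a forecast.

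The defence does not remove the double meaning. An analysis plan that settles it must depart from one half of the published sentence.

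**Conclusion.** The rule is ambiguous rather than flatly contradictory, and the ambiguity touches the primary outcome. Multiple imputation is the likelier intention. Under the carry-forward reading, the assumed 55 m difference falls by one third at 50% dropout spread evenly with linear gains, and by one fifth at 20% dropout with baseline carried. A fall of one half is the limiting case. These figures rest on the plan's assumed means and on equal, random dropout in each arm; the actual dropout rate and timing are unknown.

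The choice of tests is a lesser part of the point. The rank tests do not fit multiple imputation directly, and the classical ANOVA would lose patients if imputation were not carried through.

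**What to change.** Delete the carry-over wording and name one method. The suggested text for the primary ISWT analysis is a likelihood-based linear mixed model for repeated measures:
- data: all observed changes at weeks 4, 8 and 12;
- fixed effects: group, visit, group × visit, baseline ISWT, baseline ISWT × visit, and centre (randomisation is blocked within centre, section 2.3);
- unstructured covariance across visits;
- reported result: the week-12 contrasts between groups, with confidence intervals.

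The model uses patients with incomplete follow-up without filling in values, and replaces both the by-visit tests and the classical ANOVA for the primary outcome. Keep multiple imputation by arm as a sensitivity analysis, together with a delta-adjusted version in which dropouts' imputed values are shifted by amounts fixed in advance. If a rank test is kept for any outcome, say how it is handled across imputations.

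The cost is revised wording and modest extra analysis, with no added visits or patients, since Table 1 already schedules ISWT at every visit. The small downside is that the model assumes missing at random, which the delta-adjusted analysis probes. The change should be made before any outcome data are examined by group.

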### Study design

2.1

This study will use a multi-center, prospective, three-arm, randomized controlled trial design. The study will include patients with COPD enrolled in a multi-module MT rehabilitation group (multi-module MT group), a rhythm-guided walking rehabilitation group (rhythm-guided walking group), and a usual care group. The study period will last for 12 weeks, and the outcomes will be measured at baseline (V0), 4 weeks (V1), 8 weeks (V2), and the end of intervention (V3). A Consolidated Standards of Reporting Trials (CONSORT) flow diagram is illustrated in Figure 1. The study protocol will be reported according to the Standard Protocol Items: Recommendations for Intervention Trials 2013 (SPIRIT) (15) guidelines and the intervention procedures are described according to the CONSORT 2010 Checklists (16). The trial is registered at ClinicalTrials.gov (registration number: NCT05832814). The study schedule and assessments are summarized in Table 1.

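### Section 2.7 names a two-sample t-test for pre and post scores of the same patients, which ignores the pairing and makes the within-group results too conservative

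*Protocol article*

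**What the plan says.** Section 2.7 of the protocol article sets out three sets of tests on the outcomes.

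- **Pre/post.** "All three groups will be examined using a two-sample" Student's t-test "for normal distributions or a Wilcoxon test for non-normal distributions (pre and postscores").
- **Between groups.** "The differences among the three groups at each time point (4, 8, and 12 weeks) will be analyzed using the" Student's t-test or the Mann–Whitney U test.
- **Over time.** "A two-way analysis of variance with repeated measures will be used to determine the effects of time and group on the dependent variables".

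The threshold for all of them is a two-sided p below 0.05. Section 2.1 (Study design) shows that the measurements are repeated on the same people: "the outcomes will be measured at baseline (V0), 4 weeks (V1), 8 weeks (V2), and the end of intervention (V3"). No paired t-test is named anywhere in the article, and the Wilcoxon test is not identified as signed-rank or rank-sum.

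**The concern.** The second sentence already covers comparisons between groups, so the first is naturally read as the comparison of each group's scores before and after. Those two sets of scores belong to the same patients and will normally be positively correlated. A two-sample t-test treats them as if they came from unrelated people. It leaves the variation between patients in the error term, although the change within each patient removes it.

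An analyst who follows the sentence literally would get standard errors that are too large, confidence intervals that are too wide and p-values that are too high for the within-group changes. A real improvement within an arm could then be reported as non-significant.

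**Working it through.** **Is there a figure to reproduce?** Not on this point. The article states no standard error, no cross-sectional SD of the shuttle walk distance (ISWT) and no pre-post correlation. Its sample size rests on differences among three group means and does not use the pre/post test.

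**Inputs from the article**
- Assumed mean ISWT changes (section 2.7.1): "usual care group are 40 m, 27 m, and -15 m, respectively", with the multi-module arm first and the walking arm second.
- SDs in the same section: 35, 38 and 40 m.
- Group size: 75 patients randomized 1:1:1, so 75/3 = 25 per group.
- Significance level: 0.05, two-sided.

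**Assumptions that the article does not settle**
- The 35, 38 and 40 m are SDs of change. They are given alongside mean changes, but the text does not say so outright.
- Pre and post SDs are equal (σ).
- ρ is between 0.5 and 0.9.
- All 25 patients per group contribute, with no extra variance from imputation.

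**Formulas**
- SD of change: SD_Δ = σ√(2(1−ρ))
- Paired: SE = SD_Δ/√n
- Two-sample: SE = σ√(2/n) = SD_Δ/√(n(1−ρ))
- Ratio of two-sample to paired SE: 1/√(1−ρ)

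Worked case, multi-module arm at ρ = 0.9: σ = 35/√0.2 = 78.3 m. The two-sample SE is 78.3 × √(2/25) = 22.1 m. The paired SE is 35/√25 = 7.0 m. The ratio is 22.1/7.0 = 3.2.

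| Test | SE factor | 40 m, SD 35: SE (m) | t | 27 m, SD 38: SE (m) | t |
|---|---|---|---|---|---|
| Paired | 1 | 7.0 | 5.7 | 7.6 | 3.6 |
| Two-sample, ρ = 0.5 | 1.41 | 9.9 | 4.0 | 10.7 | 2.5 |
| Two-sample, ρ = 0.75 | 2.00 | 14.0 | 2.9 | 15.2 | 1.8 |
| Two-sample, ρ = 0.8 | 2.24 | 15.7 | 2.6 | 17.0 | 1.6 |
| Two-sample, ρ = 0.9 | 3.16 | 22.1 | 1.8 | 24.0 | 1.1 |

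**Where significance is lost.** The two-sample critical value on 48 degrees of freedom is 2.01. The two-sample t equals the paired t times √(1−ρ), so it falls below 2.01 when ρ exceeds 1 − (2.01/t_paired)².
- 40 m: 1 − (2.01/5.71)² = 0.88.
- 27 m: 1 − (2.01/3.55)² = 0.68.
- Usual care (−15 m, SD 40 m): the paired t is already only 15/8.0 = 1.9 in size, so this arm does not separate the two tests.

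**Power and type I error, walking arm.** Paired power is about 93%. For the two-sample test it is approximately Φ((27/SE − 2.01)/√(1−ρ)): about 76% at ρ = 0.5 and 32% at ρ = 0.75. The true type I error is about 2(1 − Φ(2.01/√(1−ρ))), which is 0.004 at ρ = 0.5 instead of 0.05. The error is therefore in the conservative direction.

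**The case against.** The best defence is that this is a slip of wording. Section 2.7 speaks of independent-samples t-tests where it compares dropouts with completers. It couples the between-group t-test with Mann–Whitney U but the pre/post test with Wilcoxon. That contrast suggests that a related-samples test was meant and that two-sample was used loosely for two measurements. This is plausible and lowers the likelihood that the wrong test will actually be run. It does not rescue the text: the only parametric test named for pre/post scores is the unpaired one, and Wilcoxon alone can mean either the paired or the unpaired version.

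The second defence is that little depends on this test. The same section plans between-group comparisons at 4, 8 and 12 weeks and a repeated-measures ANOVA that takes the within-patient correlation into account. Under positive correlation the error cannot produce a spurious benefit. All of this stands and limits the severity.

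A reader might also infer that efficacy will be judged by whether each arm changes significantly, so that the benefit of randomization is lost. The article does not say so. Its sample size is built on differences among the groups, and section 2.7 plans between-group tests. That reading is hypothetical.

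**Conclusion.** The point holds in a limited form. The named test is wrong for pre and post scores of the same patients, and for any positive ρ it overstates the standard error of the within-group change. The size is not fixed by the article: under the assumptions listed, the factor runs from 1.4 at ρ = 0.5 to 3.2 at ρ = 0.9, and it would differ from outcome to outcome.

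A reader might infer that the standard error is two to three times too large as a matter of fact. That needs ρ of about 0.75 to 0.89, which the article does not give. A reader might also infer that the planned 40 m improvement would be missed. That happens only above ρ of about 0.88; at ρ = 0.8 it still gives t = 2.6. The 27 m change is more exposed and loses significance above about 0.68.

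The randomized comparisons are untouched. Severity is minor to moderate.

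**What to change.** In section 2.7, replace the two-sample Student's t-test and the unspecified Wilcoxon test for pre and post scores with the paired t-test or the Wilcoxon signed-rank test. Report the within-group mean change with a 95% CI computed from the paired differences, and describe these results as supportive of the planned between-group comparisons.

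The cost is one sentence. No change to the design, sample size, data collection or other analyses is needed.

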Therefore, to identify a helpful and easy-to-use rehabilitation mode, our study aimed to develop a home-based, music-facilitated rehabilitation program for patients with COPD, using music tempo-guided walking exercises and breathing exercises, such as singing. Based on a thorough literature review, this is the first study to combine the two forms of MT for home-based PR and apply objective recording and supervision of training implementation using wearable sensors (a sports wristwatch that monitors step counts and walking distance) for music-facilitated tele-PR. This study protocol describes the process to investigate the efficacy and safety of the developed MT-facilitated telerehabilitation program (including rhythm-guided walking and singing).

The primary aim of this study is to explore the efficacy of this home-based, MT- facilitated rehabilitation program (including rhythm-guided walking and singing). The secondary aim is to explore whether addition of singing training results in improvements compared with rhythm-guided walking alone. Therefore, we hypothesize that (1) our MT-facilitated tele-PR mode could benefit patients with COPD in terms of exercise capacity, respiratory musculature, and symptoms; and (2) singing training could result in greater improvement compared with rhythm-guided walking alone.

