### Randomization, allocation concealment, and blinding

2.3

All patients will be randomized in a 1:1:1 ratio (adhering to block randomization within each center) into three groups: Multi-module MT, rhythm-guided walking, and usual care groups using a table of random numbers generated in the SPSS statistical package held by an independent statistical analyst. Group information will be stored in an opaque envelope and sealed thereafter. After obtaining informed consent and baseline assessment, the study coordinator will unseal the envelope to obtain the random numbers and grouping information for each participant.

Due to the nature of the intervention, neither the participants nor the exercise instructors will be blinded. However, pulmonology and rehabilitation nurses conducting outcome assessments and statistical analysts will be blinded to the assignments.

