### Outcome measures

2.5

Table 1 illustrates the items to be measured and the time window for data collection. The primary outcome is the exercise capacity measured by ISWT (relative change in the ISWT distance seen at 4-, 8-, and 12-weeks post-intervention compared with baseline) in all three subgroups. The ISWT will be determined according to the recommendations of the European Respiratory Society/American Thoracic Society (17). In addition, as an externally paced maximal exercise test, walking speed will be controlled by a series of pre-recorded signals. The walking speed increases progressively until the participant can no longer continue.

The secondary outcomes are:

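### The ISWT primary outcome has three co-equal visits, three arms and unadjusted two-group tests, with no primary contrast named; familywise error is about 8–29%, depending on which tests count as primary

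*Protocol article*

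**What the plan says.** Section 2.5 (Outcome measures) defines the primary outcome as the "relative change in the ISWT distance seen at 4-, 8-, and 12-weeks post-intervention compared with baseline", measured "in all three subgroups". No visit is marked as the primary one and no pair of arms is singled out.

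Section 2.7 (Statistical analysis) gives the between-group comparison, by t-test or Mann–Whitney test: "The differences among the three groups at each time point (4, 8, and 12 weeks) will be analyzed using the" (the sentence ends by naming those two tests). It adds a second analysis: "A two-way analysis of variance with repeated measures will be used to determine the effects of time and group on the dependent variables". The section does not say which of the two decides the primary outcome, or that one must be significant before the other is read. The threshold is common to all tests: "Statistical significance is set at two-sided" p < 0.05.

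The Introduction ranks the aims. "The primary aim of this study is to explore the efficacy of this home-based, MT- facilitated rehabilitation program"; no comparator is named. "The secondary aim is to explore whether addition of singing training results in improvements compared with rhythm-guided walking alone".

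Section 2.7.1 (Sample size calculation) uses a single k-group formula for mean ISWT change at α = 0.05.

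**The concern.** A t-test or Mann–Whitney test compares two groups. With three arms it can only be applied pair by pair, so the plan as written gives 3 pairs × 3 visits = 9 tests on the primary outcome, each at 0.05. Nothing says which of them answers the primary question. A single p-value below 0.05, for instance at week 4 in one pair, could be reported as a positive primary result.

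This is more than detail left to an analysis plan. The article states three equal visits, two-group tests for three arms and a flat 0.05. It also plans the sample size on one overall comparison, so the α used for planning does not describe the tests that will be read.

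**Working it through.** **1. The plan's own figure.** The article states no familywise error rate. Its only related figure is the 18 per group in section 2.7.1, from assumed mean changes of 40, 27 and −15 m and SDs of 35, 38 and 40 m.

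- Grand mean = (40 + 27 − 15)/3 = 17.33 m.
- Squared deviations = 513.8 + 93.4 + 1045.4 = 1652.7. Between-group variance = 1652.7/2 = 826.3.
- Mean within-group variance = (35² + 38² + 40²)/3 = 1423.
- One-way ANOVA (noncentral F, α = 0.05): 12 per group gives power 0.901, which matches the stated β = 0.1. Then 12 × 1.5 = 18.

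The 18 is therefore reproduced by one overall three-group test at 0.05, not by nine pairwise tests.

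**2. Inputs for the error rate.**

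- Arms: 3, allocated 1:1:1 (section 2.3). With 75 enrolled this is 25 per arm, or 12.5 if half drop out (section 2.7.1).
- Visits: 4, 8 and 12 weeks (section 2.5).
- Level: two-sided 0.05 per test (section 2.7).
- Between-visit correlation ρ of the change scores: not in the article. Assumed equal across visits and varied from 0.5 to 0.9, with the extremes also shown.

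**3. Reference value.** Nine independent tests would give 1 − 0.95⁹ = 0.370. The real tests share arms and patients, so this is too high and simulation is needed.

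**4. Simulation under the global null.** Correlated normal change scores, pooled t-tests at 0.05, 20,000 trials per setting, 25 per arm. Entries are the chance of at least one p < 0.05.

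| Tests counted as primary | ρ = 0.5 | ρ = 0.7 | ρ = 0.9 |
|---|---|---|---|
| All 3 pairs × 3 visits (9) | 28.8% | 24.7% | 19.1% |
| Both active arms vs usual care × 3 visits (6) | 22.3% | 19.0% | 14.7% |
| MT vs usual care × 3 visits (3) | 12.7% | 11.0% | 8.2% |
| All 9, read only after a significant ANOVA group or interaction test (not stated in the plan) | 8.4% | 6.9% | 6.0% |

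With 12 per arm the nine-test figures are 29.1%, 25.4% and 19.6%, so sample size hardly matters. At the extremes of ρ the nine-test figure is 32% (ρ = 0) and about 12% (ρ = 1).

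**5. What fixing the visit alone achieves.** At week 12 only, all three pairs give about 12%, and both active arms against usual care about 9%. One contrast at one visit gives 5%.

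**6. Power of a single primary contrast, on section 2.7.1's figures.** For MT vs usual care the difference is 40 − (−15) = 55 m. With 12.5 per arm, SE = √[(35² + 40²)/12.5] = √226 = 15.03 m, so the noncentrality is 55/15.03 = 3.66. On 23 degrees of freedom (critical t = 2.069) power is about 94%. With 25 per arm it exceeds 99%. Bonferroni over nine tests (0.05/9 = 0.0056 each) would cut the 12.5-per-arm figure to about 72%.

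**The case against.** The strongest reply is that nine is not the right count. The Introduction makes MT against walking alone a secondary aim, and the Discussion concedes that this contrast may not reach significance on ISWT. Three of the nine tests then fall outside the primary question. This stands. A reader might infer that 19–29% is the trial's false-positive rate, but the documents support it only as one reading. It follows from section 2.5, which keeps all three arms in the primary outcome, and it depends on a correlation the article does not supply. The narrower families still exceed 5%.

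A second reply is that the repeated-measures ANOVA, together with the three-group sample size formula, implies an overall test first. If it gated the pairwise tests, the error would fall to about 6–8%. Section 2.7 does not say so; it lists the ANOVA after the pairwise tests and gives it no priority.

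Third, both aims are worded as exploration, section 2.7.1 disclaims a formal sample size calculation, and the Discussion calls the trial a pilot. This lowers the consequence. It does not remove the problem, because the article also states directional hypotheses, a power target and a significance threshold.

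Finally, a reader might infer that no outcome other than the primary one may carry a significance test. The documents do not support that. The Discussion places the expected gain from singing in respiratory muscle function and mental health, so hypothesis 2 needs tests on those outcomes.

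**Conclusion.** The concern holds as a defect in the stated plan: two-group tests for three arms, three equal primary visits, a flat 0.05, and no primary contrast or ranking of the ANOVA against the pairwise tests. Under the global null and an assumed between-visit correlation of 0.5–0.9, the chance of at least one false-positive ISWT result is about 19–29% for all nine tests, 15–22% for both active arms against usual care, and 8–13% for MT against usual care. Which range applies cannot be settled from the article, because it does not say which tests are primary. Over the assumed correlations every one of these readings exceeds 5%; only the limit of one contrast with perfectly correlated visits returns to it. Given the pilot and exploratory framing, this should be fixed but does not by itself invalidate the trial.

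**What to change.** In sections 2.5 and 2.7:

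- Name one primary test: ISWT change at 12 weeks, multi-module MT against usual care, two-sided 0.05.
- Then test walking against usual care, and last MT against walking, both at 12 weeks and at 0.05, in that fixed order and stopping at the first non-significant result. This holds the familywise error of the three at 5%.
- Report ISWT at 4 and 8 weeks as supportive, with estimates and 95% confidence intervals.
- State the role of the repeated-measures ANOVA relative to these tests.
- Label tests on secondary outcomes, including respiratory muscle function and mental health for hypothesis 2, as secondary and not adjusted for multiplicity.
- Reconcile the relative change in section 2.5 with the changes in metres assumed in section 2.7.1. The 94% power figure applies only to the latter.

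The cost is a paragraph of text and a matching registry update. The trial gives up any confirmatory claim at 4 or 8 weeks. On the article's own assumptions in metres, power for the primary contrast stays at about 94% even with half the patients lost.

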**Figure 1 fig1:**
[figure not shown]
Flow diagram of study design.

**Table 1 tab1:** Summary of study schedule.

	Enrolment	Baseline (V0)	4 weeks (V1)	8 weeks (V2)	12 weeks (V3)
Eligibility screening					
Informed consent	√				
Randomization		√			
Allocation		√			
Interventions					
Multi-module music therapy					
Rhythm-guided walking					
Usual care					
Assessments					
Demographic characteristics		√			
ISWT		√	√	√	√
MIP; MEP		√	√	√	√
Spirometry		√			√
SPPB		√	√	√	√
mMRC; CAT		√	√	√	√
SGRQ; EQ-5D		√	√	√	√
HADS		√	√	√	√
IPAQ		√	√	√	√
Training adherence			√	√	√
AEs			√	√	√

ISWT, incremental shuttle walking test; MIP, maximal inspiratory pressure; MEP, maximal expiratory pressure; SPPB, Short Physical Performance Battery; mMRC, Modified Medical Research Council; CAT, COPD assessment test; SGRQ, St. George’s Respiratory Questionnaire; EQ-5D, EuroQoL-5D Questionnaire; HADS, Hospital Anxiety and Depression Scale; IPAQ, International Physical Activity Questionnaire; AE, adverse event.

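### The planned between-group tests adjust for neither baseline nor centre, and do not say which score or which ANOVA effect answers the question: a modest precision loss if change is analysed, a larger one if raw scores are

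*Protocol article*

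**What the plan says.** Section 2.7 (Statistical analysis) plans two between-group procedures. The first is a Student's t-test or Mann–Whitney U test at each of weeks 4, 8 and 12. The second is described in one sentence: "A two-way analysis of variance with repeated measures will be used to determine the effects of time and group on the dependent variables". Neither is given a baseline covariate or a centre term, and no group-by-time contrast is named. The section refers to scores and dependent variables. It does not say whether distances or changes are compared between groups, or whether V0 is one of the repeated visits.

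Other sections bear on this:

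- Section 2.3 randomizes 1:1:1, "adhering to block randomization within each center".
- Section 2.1 and Table 1 place ISWT and nearly all other outcomes at V0, V1, V2 and V3, so a baseline value exists for every patient.
- Section 2.5 defines the primary outcome as relative change in ISWT distance from baseline at the three later visits. It defines no change score for the secondary outcomes.
- Section 2.7.1 sizes the trial on mean changes: those of the multi-module music therapy (MT), rhythm-guided walking and "usual care group are 40 m, 27 m, and -15 m, respectively", and "the combined standard deviations (SD) are 35 m, 38 m, and 40 m, respectively".

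**The concern.** Baseline walking distance is usually the strongest predictor of later walking distance, and centre is a design factor here. A plan that collects one and blocks on the other, but names tests that use neither as an adjustment, gives up precision that costs nothing to keep.

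The wording also admits several different analyses. A t-test on change, a t-test on raw week-12 distance and an ANOVA group main effect over four visits can have very different power for the same data. The ANOVA main effect may not even estimate the week-12 difference. If V0 is one of its levels, it averages in a visit at which no treatment effect can exist, and the treatment effect then lies in the group-by-time interaction, which the sentence does not name. Tests that disagree would leave the choice of result open.

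**Working it through.** **Inputs from the article.** Mean changes 40, 27 and −15 m; SDs 35, 38 and 40 m, read as SDs of change (section 2.7.1). "Based on a rate of type-I error of α = 0.05" (section 2.7.1), two-sided (section 2.7). 75 patients, so 25 per arm. A 50% dropout allowance leaves about 12 per arm.

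**Assumption.** The baseline–follow-up correlation ρ of ISWT is not given. I take 0.5 to 0.95, with equal variance at all visits and equal correlation between visits.

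**The plan's own figure.** I read the sample size formula with squared deviations, because unsquared ones sum to zero.

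- Mean variance: (35² + 38² + 40²)/3 = 1423.
- Grand mean 17.33 m; sum of squared deviations 1652.7; divided by k − 1 = 2 this is 826.3.
- With ψ = 2.195 (80% power): n = 2.195² × 1423/826.3 = 8.30, rounded up to 9; 9/(1 − 0.5) = 18.

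The stated 18 per group reproduces, so the sizing is in terms of change in metres. (The text gives "a power of 80% (rate of type-II error of β = 0.1"), which is inconsistent, but nothing below depends on it.)

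**SDs for MT against usual care.** The difference is 40 − (−15) = 55 m. The pooled SD of change is √((35² + 40²)/2) = 37.6 m.

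- Raw score SD: σ = 37.6/√(2(1 − ρ)).
- Baseline-adjusted SD: σ√(1 − ρ²).
- SD of a four-visit mean: σ√((1 + 3ρ)/4).

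**Reading A: change is analysed.** The ratio of adjusted variance to change-score variance is (1 − ρ²)/(2(1 − ρ)) = (1 + ρ)/2. This is 0.75 at ρ = 0.5, 0.90 at 0.8, 0.95 at 0.9 and 0.975 at 0.95. Power for 55 m (noncentral t):

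| Per arm | t-test on change | Baseline-adjusted, ρ = 0.8 to 0.95 |
|---|---|---|
| 25 | 99.9% | over 99.9% |
| 12 | 93% | 95% to 93% |

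**Reading B: raw week-12 distance is tested.**

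| ρ | σ (m) | Power, 25 per arm | Power, 12 per arm |
|---|---|---|---|
| 0.5 | 37.6 | 99.9% | 93% |
| 0.8 | 59.4 | 89% | 58% |
| 0.9 | 84.0 | 62% | 34% |
| 0.95 | 118.8 | 36% | 19% |

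At ρ = 0.5 this test equals the change test, so the large losses need a high correlation.

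**Reading C: the ANOVA group main effect on raw distance, with V0 as a level of time.**

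- Full effect from V1: 55 × (0 + 1 + 1 + 1)/4 = 41.25 m.
- Linear build-up to V3: 55 × (0 + 1/3 + 2/3 + 1)/4 = 27.5 m.

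Power at 25 per arm for ρ = 0.8, 0.9 and 0.95 is 74%, 42% and 23% (full from V1), or 41%, 22% and 13% (linear). If changes at V1–V3 are analysed instead, no pre-treatment visit is averaged in. A linear build-up still averages to (1/3 + 2/3 + 1)/3 = 2/3 of the week-12 effect.

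**Centre.** The article gives no between-centre variance, so the effect of leaving centre out cannot be calculated.

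**The case against.** The strongest reply is that baseline is already used. Section 2.5 defines the primary outcome as change from baseline, and section 2.7.1 sizes on mean changes. On that reading the plain t-test has 99.9% power for 55 m at 25 per arm, and adjustment has almost nothing left to add for that contrast. This stands, and it limits the finding for ISWT to a variance saving of 2.5% to 25%. It does not carry over to the secondary outcomes, for which no change score is defined and a visit-wise test most naturally uses raw scores.

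A second reply is that a two-way repeated-measures ANOVA ordinarily contains the interaction, that listing model terms belongs in an analysis plan, and that the week-12 comparison is made by the visit-wise tests anyway. This stands in part: the interaction is unnamed, not excluded. But section 2.7 does name the tests and the effects of interest, and what it names is unadjusted.

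A reader might infer more than the article supports:

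- That the analysis ignores baseline altogether. It does not, given the definition of the primary outcome.
- That unadjusted tests dilute the treatment effect. They do not: in a randomized trial the unadjusted mean difference is unbiased. Shrinkage arises only in the ANOVA main effect, and only if V0 or early visits enter it.
- That omitting centre biases the estimate or makes the tests too liberal. Leaving out a stratification factor tends to make standard errors too large.

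**Conclusion.** The point holds as a matter of precision and clarity. Section 2.7 commits to between-group tests with no baseline covariate and no centre term, despite baseline data on everyone and blocking within centre. It leaves open which score is tested and which ANOVA effect is the efficacy result.

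The size depends on the reading. If change in ISWT is analysed, the better supported reading for the primary outcome, the loss is modest and does not threaten power for 55 m. If raw scores are tested, power for 55 m at 25 per arm falls to between 89% and 36% for ρ from 0.8 to 0.95. The reduction of 55 m to 41 m or 27.5 m applies only with V0 in the time factor. These figures rest on the assumed ρ, on equal variances and correlations across visits, and on change in metres; a percentage reading of relative change was not worked through. The loss from omitting centre has a likely direction but no computable size.

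**What to change.** For ISWT and the other continuous outcomes measured at V1–V3, replace the set of t-tests and ANOVA by one mixed model for repeated measures on V1–V3, with group, visit, group × visit, baseline value, baseline × visit and centre. Small centres may be pooled by a rule set in advance. Alternatively, and for an outcome such as spirometry that is measured only at V0 and V3, use an ANCOVA at V3 with baseline and centre.

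Name the 12-week group contrasts (MT against usual care first, then the others) and report each with a 95% confidence interval. State the variable analysed. With V0 as a covariate it is no longer a level of time, so the question of averaging in a pre-treatment visit disappears.

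The cost is wording in the analysis plan and a little more analysis work. No new data, visits or patients are needed.
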